### 2.13. Data Management

Standardised data collection forms are entered into Research Electronic Data Capture (REDCap, Vanderbilt University Medical Centre, Institute for Clinical and Translational Research, hosted by University of Auckland, Auckland, New Zealand) by an administrator [29].

A data safety monitoring committee (DSMC) was established.

### 2.14. Statistics

Initial chi-square tests for categorical data. Numeric data are to be analysed with Mann–Whitney non-parametric statistics or t test if normally distributed. Secondary analysis is planned using logistic regression (IBM SPSS Statistics 26, IBM Corporation 2020, New York, NY, USA). Two-sided probability (*p* value) < 0.05 will be used to indicate statistical significance.

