### 2.6. Outcome Measures

The primary outcome is red blood cell transfusion rates during the neonatal admission. The proportion of infants transfused as well as the number of transfusions and volume of blood transfused will be compared, with the primary comparison being the proportion transfused in either group. The study centre transfusion guideline will remain unchanged during the planned study period (Table A1 in Appendix A). Infants who receive a transfusion at a surgical centre will be recorded separately to avoid the problem of differing blood transfusion guidelines.

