### 2.8. Sample Size

Data from an observational study indicated that 60% of infants that received DCC and did not breathe received a blood transfusion. This compared to 30% transfused in the group that breathed during DCC. Aiming for a similar 50% relative reduction in the proportion transfused would require 100 infants whose primary outcome could be assessed. To allow for cases where outcome assessment may not be possible (deaths, surgical transfer), 120 infants are to be randomised (60 per group). (A total of 100 would give the study 85% power at a two-sided significance level of 0.05). For a secondary composite outcome of death, CLD or severe IVH, the sample size would allow a 36% difference in outcome to be detected (80% power, significance 0.05), assuming the percentage of infants with a composite endpoint will be 58% (based on historic data).

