### 2.9. Intervention Assignment

Sequence generation: One-to-one allocation to study groups based on computer generated randomisation sequences with random block sizes. Groups will be stratified into ≤26, >26 and <28 weeks and ≥28 to <31 weeks gestation.

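### The chi-square for the primary outcome ignores the gestation bands used to stratify randomisation; if gestation predicts transfusion, the test is conservative and gives up some power

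*Protocol article*

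**What the plan says.** Section 2.9 of the protocol article describes the allocation: "One-to-one allocation to study groups based on computer generated randomisation sequences with random block sizes", and then "Groups will be stratified into ≤26, >26 and <28 weeks and ≥28 to <31 weeks gestation".

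Section 2.6 makes the primary outcome binary, "with the primary comparison being the proportion transfused in either group". Section 2.14 gives the tests. For a binary outcome the relevant line is "Initial chi-square tests for categorical data", with no mention of strata. The only model-based analysis is placed second: "Secondary analysis is planned using logistic regression", with no covariates named.

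Section 2.8 sets the planning rates: "60% of infants that received DCC and did not breathe received a blood transfusion", and "This compared to 30% transfused in the group that breathed during DCC". It concludes that this "would require 100 infants whose primary outcome could be assessed" and states 85% power at a two-sided 0.05. It plans to randomise 120 to allow for deaths and surgical transfers.

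**The concern.** Blocked allocation within gestation bands makes the two arms more alike on gestation than simple randomisation would. The between-band part of the variation in transfusion is then largely removed from the difference between arms. The pooled chi-square variance still contains it. If the bands differ in transfusion risk, the standard error is too large, the p-value is too high, and an interval built on the same variance is too wide.

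What is at stake is efficiency. The trial takes the trouble to balance on gestation and then does not collect the benefit in its main comparison. The text also leaves open which result governs if the initial crude test and the secondary regression disagree.

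**Working it through.** **1. The plan's own figure.** Inputs from section 2.8: rates 0.60 and 0.30, 50 assessable infants per arm, two-sided 0.05. With a mean rate of 0.45,

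z = [0.30·√50 − 1.96·√(2·0.45·0.55)] / √(0.60·0.40 + 0.30·0.70) = (2.121 − 1.379) / 0.671 = 1.107,

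and Φ(1.107) = 86.6%. The stated 85% reproduces, and it belongs to an unadjusted comparison.

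**2. Assumptions.** The article gives no transfusion rates and no shares of infants by gestation band. Band shares are taken as 25/25/50% (≤26, >26 to <28, ≥28 to <31 weeks). The rates by band are varied while the overall rate is held at 60%.

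**3. Large-sample type I error of the unadjusted test.** With shares s and rates p by band and overall rate P,

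R = Σ s·p(1 − p) / [P(1 − P)], and type I error ≈ 2·[1 − Φ(1.96/√R)].

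- Moderate effect (85/70/42.5%): R = (0.0319 + 0.0525 + 0.1222)/0.24 = 0.861, giving 3.5%.
- Strong effect (95/75/35%): R = (0.0119 + 0.0469 + 0.1138)/0.24 = 0.719, giving 2.1%.

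**4. Simulation.** Each setting used 8,000 trials (Monte Carlo standard error about 0.24 points at 5%). In each trial 120 infants were randomised in blocks of 2, 4 or 6 within bands, and each infant was assessable with probability 100/120. Pearson chi-square was compared with Cochran-Mantel-Haenszel (CMH) over the three bands, both without continuity correction. For power, a common odds ratio within bands lowers the overall rate from 60% to 30%.

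| Assumed rates by band | Type I, Pearson | Type I, CMH | Power, Pearson | Power, CMH | Difference (points) |
|---|---|---|---|---|---|
| None: 60/60/60% | 5.2% | 5.0% | 87.1% | 86.8% | −0.3 |
| Mild: 72/66/51% | 5.1% | 5.2% | 86.5% | 87.0% | +0.5 |
| Moderate: 85/70/42.5% | 4.2% | 5.3% | 88.5% | 91.3% | +2.8 |
| Strong: 95/75/35% | 2.7% | 5.1% | 89.6% | 96.0% | +6.4 |
| Very strong: 98/85/28.5% | 1.5% | 4.5% | 91.6% | 98.5% | +6.9 |

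With an overall rate of 45%, the unadjusted type I error was 3.7% (70/50/30%) and 2.8% (85/55/20%), against 4.6% and 5.3% for CMH. The simulated values lie somewhat above the large-sample ones in most settings, as expected when incomplete blocks and random losses leave some imbalance. A separate run of the same design gave 4.3% for a moderate and 2.4% for a strong effect.

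**5. Smaller true effects.** A separate simulation used 100 infants and band shares of 25/20/55%. For a 15-point fall, power was 32% (Pearson) versus 46% (CMH) with strong rates of 95/80/37%, and 34% versus 36% with weaker rates of 85/70/45%.

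**The case against.** The strongest reply has four parts.

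- **The size is assumed.** A reader might infer that the chi-square is known to run well below 5%. The documents do not support that. Section 2.8 reports transfusion by breathing status only. Table A1 ties transfusion to haemoglobin and clinical state, including respiratory support, and not to gestation. With a mild gestation effect the test sits at about 5%. This part stands, and the size must be stated conditionally.
- **The plan meets its own target.** A reader might infer that the trial is underpowered because it omits the strata. It is not: the 85% was computed for an unadjusted comparison, and the uncorrected Pearson test reached it in every setting tried. This stands. A Yates correction, if used, would give 82.9% by exact calculation at 50 per arm, but that is a separate choice which the article does not settle.
- **The largest gain needs two assumptions.** The 32% versus 46% contrast requires both strong band rates and a 15-point effect that the protocol does not plan for. It shows that the gain can be larger for smaller effects and should not be the headline. The introduction does cite smaller reductions (10%, and 54% to 47%), but those trials compared delayed with early clamping, not the two arms here.
- **The error is in the safe direction, and a regression is already planned.** Both are true. The article is condensed, and naming covariates may be left to a fuller plan. But section 2.14 does fix the order, crude first and modelled second. That order is the point at issue, not a missing detail.

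**Conclusion.** The mismatch between a stratified design and an unstratified primary test is real, and its direction is clear: conservative if gestation is prognostic. Its size cannot be fixed from the documents. Under the assumed rates, type I error ranges from about 5% (no or mild effect) through about 4% (moderate) to 2–3% (strong), and 1.5% in the most extreme case. Power forgone at 60% versus 30% is nil to half a point, about 3 points, and 6–7 points respectively.

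This mechanism does not inflate false positives, and the primary conclusion would not be invalid. The results rest on the assumed band shares and rates, a common odds ratio across bands, losses unrelated to arm or outcome, and independent infants. Multiples are randomised individually (section 2.10); sibling correlation was not simulated and could change the type I error. The point is a recommended efficiency improvement.

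**What to change.** In section 2.14, state that the primary comparison of the proportion transfused is stratified by the three randomisation bands, by CMH or by regression with band as a covariate. Report a stratum-adjusted risk difference or risk ratio with a 95% CI, and keep the crude chi-square as a supportive analysis.

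The cost is one sentence. The band is already recorded for every randomised infant, since it determines the envelope. If gestation turns out not to be prognostic, the loss is at most about half a point of power (0.3 in the table), and CMH stayed between 4.5% and 5.3% type I error in every setting tried.

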### 2.15. Ethics

Written informed consent will be obtained before labour where possible. In cases where active labour is in progress; and consent before birth is not possible, approval was obtained from the Northern A Health and Disability Ethics Committee, New Zealand (15/NTA/146AM01) as well as the following local groups to allow randomisation at birth, and obtain postnatal consent for the collection of outcome data: Māori Health Ethics committee, Patient Whanau Centred Care Consumer Council, Maternity consumer group, organisational legal opinion, parental input from Neonatal Unit parents of preterm infants as well as Neonatal, Midwifery, Obstetric and Anaesthetic department stakeholders. In cases where antenatal consent could not be obtained and parents decline consent, the initial data capture sheet will be discarded, and no further data collected.

## Figures and Tables

**Figure 1 children-08-00336-f001:**
[figure not shown]
ABC Study flow diagram.

## Appendix A

**Table A1 children-08-00336-t0A1:** Hospital blood transfusion guideline.

Haemoglobin (Hb) (Haematocrit)	Consider Transfusion
Hb < 70 g/L (Haematocrit ≤ 20%)	Symptomatic anaemia: any of the following without obvious cause: Significant apnoea and bradycardia while receiving caffeine (>9 episodes in 12 h or 2 episodes in 24 h requiring bag mask ventilation). Heart rate > 170 beats per minute or respiration rate > 70 breaths per minute persists for 24 h. Poor weight gain (< 10g/day over 7 days). Increasing ductal shunt and cardiac decompensation. Any positive pressure support. Asymptomatic with reticulocytes < 100,000 × 10^9^/L.
Hb 70–80 g/L (Haematocrit 21–25%)	Symptomatic anaemia as above. CPAP with FiO_2_ 0.25–0.4. Undergoing surgery.
Hb 81–100 g/L (Haematocrit ≤ 25–30%)	CPAP with FiO_2_ > 0.4. Mechanical ventilation with MAP ≥ 7–10 cm H_2_O.
Hb 101–110 g/L (Haematocrit ≤ 21–25%)	Critically unwell with one or more of the following: CPAP and FiO_2_ > 0.4. Ventilation MAP > 10 cm H_2_O. Acute bleeding.
